#### Anthropometric measurements

A stadiometer is used to measure height, a validated digital scale for weight, and a tape measure specifically designed for accurate and repeatable measurements of various body dimensions for waist circumference. All height and waist circumference measurements are recorded to the nearest 0.1 cm and all weight measurements are recorded to the nearest 0.1 kg respectively. All measurements are taken without shoes and with light clothes.

#### Electronic health record data

Patients’ electronic health records (EHRs) are reviewed following each study visit to extract information regarding hypertension characteristics and treatment (that is, medications, dosages, and physician notes), comorbidity, and relevant lab results (that is, blood glucose, lipids). EHRs are also the source of information for certain cost data, including direct costs to third party payers.

#### Cost data

In addition to expenses associated with implementation of the two interventions, cost measures include resource costs associated with direct health care costs, including use of ambulatory care services, such as physician and ED visits, laboratory tests, hospitalizations, surgical procedures, and medication regimens. Intervention costs will include all direct (labor) and indirect (overhead) incremental costs associated with implementation of the interventions - most notably, labor and equipment costs associated with HBPTM, costs of producing and distributing educational materials, and costs associated with the NCM’s time. Unit costs of interventions will be measured by detailed resource-cost analyses of the time of involved health professionals and supplies or equipment. Utilization of health care services is obtained from EHRs and patient surveys. The unit costs of ambulatory services are obtained from clinic billing records and the costs of medications from prescribed regimens and the Red Book prices for the prevailing years.

### Sample size and power analysis

The primary hypotheses are (a) a greater reduction in systolic BP over three waves of data: baseline, 6 and 12 months and (b) a lower 24-month stroke recurrence rate among the combined HBPTM + NCM group compared to the HBPTM alone group. Although there may be more than one episode of stroke per patient, given the sample size, we will combine all events. We assume separate analyses of the outcomes, with pre-specified α = 0.05 for each outcome. Statistical modeling procedures will be used that allow the inclusion in the analysis of participants who do not complete the follow-up assessment (on an intent-to-treat basis). The approach to the power calculations incorporates the design feature of clustering. The cluster size of participants who are eligible (uncontrolled hypertension with a history of stroke) within PCP is estimated to range from 5 to 6. Data from a similar study of telemedicine (IDEATel) delivered to New York City Hispanics and Blacks did not show heterogeneous variances [60], so this scenario was not included in power calculations. Specific types of selection bias and attrition were considered.

Based on studies of telemedicine in Blacks and Hispanics [42,43,60-62], it was estimated that the baseline and longitudinal standard deviations of SBP at baseline will be between 18 and 22 mm Hg. The observed mean differences were from 3 to 8 for SBP. We posited that the enhanced telemedicine intervention will result in an effect size ranging from a 6- to 8-point difference in SBP. The assumptions were as follows: α = .05 for a two-tailed test; 1-β = .80 and above; and δ = μ_1_-μ_2_ = 6, 7, 8 (SBP point reduction). The following assumptions were used in the power calculations: R = 0.90 (reliability); g = 2 (groups), pooled σ = 20.75 (baseline control: 19.6; intervention 19.2; 6 month control: 21.7; intervention: 20.5; 12 month control: 21.0; intervention: 22.3), d = δ/σ (where δ is difference in end study and d is Cohen’s d;) [63]. The cluster size was estimated as 5; the intracluster correlation (ICC) = 0.03; and Vif = 1+ (clustersize-1)*ICC = 1.12.

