#### Screening and baseline visits

All interactions between the RA and the patient are in English or Spanish, depending on the patient’s preference. After obtaining written informed consent, the RA takes three BP measurements using the Microlife Watch BP Office, a validated automated BP device (see www.dableducational.org), following American Heart Association guidelines [48]. Patients with an average SBP ≥140 mm Hg are scheduled for a second eligibility visit within 3 to 14 days, at which time a second BP measurement is taken. Patients must have an average SBP ≥140 mm Hg at each of the two screening visits to be eligible. To assess other eligibility criteria, the RA administers a computer-assisted personal interview (CAPI) programmed by the Research Core (see Data Management section below), which includes the CARE-Diagnostic Scale, modified Rankin Scale and other self-report items. Patients who are eligible are scheduled for a baseline visit, at which time the RA takes measurements of height, weight, waist circumference and BP and administers the baseline interview; self-report measures included in this interview are listed in the Study Measures section below.

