### Study measures

The primary outcomes are within-patient change in SBP from baseline to 12 months and stroke recurrence rates at 24 months. Secondary outcomes are 12- and 24-month cost-effectiveness. Exploratory outcomes include 1) physicians’ hypertension medication intensification [49]; (2) patients’ health behaviors (diet, physical activity, medication adherence); and (3) other important stroke risk factors (blood glucose, lipids).

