### Power for comparing rates of change in systolic blood pressure response over 12 months between groups

The power to detect a difference in slopes (β_1A_-β_1B_) over the twelve months of the study (using all waves of data) was examined. An estimate of the required sample sizes [64,65], is given, considering time measured as the duration between the first and jth occasion, j = 0, 0.5, 1 year. The assumptions above were used regarding design effects and reliability; these calculations assume that ρ = 0.5, 0.6 (the average correlation between baseline and follow up) and δ = 6, 7 (SBP = yearly point reduction). Based on examination of endpoint differences, the required sample sizes ranged from 175 to 225, depending on the assumptions regarding effect sizes [66]. The selected sample size of 225 per group permits detection of relatively small effect sizes, ranging from 5 to 6, depending on different scenarios.

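### Screening SBP from two pre-randomisation visits has no stated role in the primary SBP analysis: a modest, assumption-dependent precision gain is left unused

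*Protocol article*

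**What the plan says.** Under Inclusion criteria, screening SBP is the average of three readings at each of two visits. Screening and baseline visits adds: "Patients must have an average SBP ≥140 mm Hg at each of the two screening visits to be eligible". The second visit falls 3 to 14 days after the first. Patients who qualify then attend a separate baseline visit, where the research assistant measures BP again. Under Randomization, allocation follows completion of the baseline assessments and confirmation of the stroke diagnosis. Each randomised patient therefore has three SBP visit values from before allocation. The validated automated device named for the first screening visit is also the one named for study visits under Blood pressure, where a visit's SBP is the mean of three readings.

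For the analysis, Study measures states: "The primary outcomes are within-patient change in SBP from baseline to 12 months". The Sample size section limits the SBP hypothesis to "a greater reduction in systolic BP over three waves of data: baseline, 6 and 12 months". The Analytic plan specifies a mixed model in group, time and their interaction, and says that the main treatment-effect analyses are not planned to include covariates. The document assigns the two screening values no use other than deciding eligibility.

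**The concern.** SBP at one visit is a noisy measure of a patient's usual SBP. Two further protocol-standard measurements, required of everyone enrolled, carry information about the 12-month value that the stated primary analysis does not use. Because they precede randomisation, using them as a covariate cannot bias the comparison between arms. At stake is the precision of the SBP co-primary. At the smallest hypothesised difference, 6 mm Hg, the planned change analysis sits close to its 80% power target under the less favourable correlation assumption.

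**Working it through.** **Inputs from the protocol article (Sample size and power sections)**

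- Error rates: "α = .05 for a two-tailed test; 1-β = .80 and above".
- SD: "pooled σ = 20.75". The root mean square of the six listed SDs is 20.745, so this reproduces.
- Correlation of baseline with follow-up (ρ): 0.5 or 0.6.
- Reliability: 0.90. Clustering inflation: 1.12. Difference: 6 mm Hg. Group size: 225.
- Not given: the correlation r between the pre-randomisation visits. It is assumed below and varied.
- No dropout rate is stated, so none is applied.

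**Step 1. The plan's own figure.** With times 0, 0.5 and 1 year and constant correlation, the slope comparison equals a comparison of 12-month change, with variance 2(1−ρ)σ².

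- Unadjusted n per group at ρ = 0.5, δ = 6: 2 × (1.96 + 0.8416)² × 20.75² × 1 / 6² = 188. Multiplying by 1.12 gives 210, and dividing by 0.90 gives 234. The plan's upper figure of 225 lies between 210 and 234.
- At δ = 7, ρ = 0.5, the fully inflated n is 172, against the plan's lower figure of 175.
- Power at 225 per group, δ = 6, ρ = 0.5: SE = 20.75 × √(1.12/0.90) × √(2/225) = 2.182, and Φ(6/2.182 − 1.96) = 0.785. At ρ = 0.6 it is 0.867.

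The stated power of at least 0.80 is thus approximately reproduced.

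**Step 2. Adjusting for the baseline visit alone.** Residual variance is (1−ρ²)σ². At ρ = 0.5 this is 0.75σ², SE = 2.182 × √0.75 = 1.890, and power is 0.888. At ρ = 0.6 power is 0.930.

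**Step 3. Adjusting for the mean of three visits, ignoring selection.** Residual variance is [1 − 3ρ²/(1+2r)]σ². Reduction relative to step 2:

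| r | ρ = 0.5 | ρ = 0.6 |
|---|---|---|
| 0.6 | 12.1% | 20.5% |
| 0.7 | 8.3% | 14.1% |
| 0.8 | 5.1% | 8.7% |
| 0.9 | 2.4% | 4.0% |

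The last row applies if the plan's reliability is read as the between-visit correlation.

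**Step 4. Allowing for selection at 140 mm Hg.** Simulation kept only patients with both screening values at or above 140, and only scenarios whose enrolled patients resembled the plan's assumptions (baseline SD about 17-22, baseline-to-12-month correlation about 0.5-0.6). Relative to step 2, the residual variance ratio ran from 0.80 to 0.97. Where true SBP tracked imperfectly over 12 months (true-value correlation 0.7 to 0.85), the reduction was about 3-10%. It exceeded about 10%, reaching about 20%, only with perfect tracking.

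**Step 5. Power with the three-visit mean (δ = 6, ρ = 0.5, 225 per group).**

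- 3% reduction: SE = 1.890 × √0.97 = 1.861, power 0.90.
- 10% reduction: SE = 1.890 × √0.90 = 1.793, power 0.92.
- 20% reduction: SE = 1.890 × √0.80 = 1.690, power 0.94.

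In patients, 3-10% is worth 450 × (1/0.97 − 1) = 14 to 450 × (1/0.90 − 1) = 50 on 450.

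**The case against.** The strongest reply is that nothing here is wrong. A baseline visit kept apart from visits selected at 140 mm Hg or above is sound practice, because it limits regression to the mean in the reported within-patient change. A group-by-time mixed model is a legitimate analysis. That stands, and it is why the baseline visit should remain the reference for descriptive change.

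A reader might infer that the screening values are thrown away. The document does not say so. It gives them no role in the primary analysis as stated, and an analysis plan that is not shown could still use them.

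A reader might also quote a definite gain, such as 8-17%. Figures of that size follow from some choices of r, or from patients keeping their relative true SBP almost unchanged for a year. The document gives no r, and both arms receive a 12-month BP intervention, so perfect tracking is a generous assumption. The only reliability stated, "R = 0.90 (reliability", would imply 2-4% if it meant agreement between visits, but the text does not say what it refers to.

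Finally, it is tempting to argue that the SBP comparison is short of power and that the screening visits supply it. That mixes two comparators. The thin margin (0.785) belongs to the unadjusted change analysis. Once the baseline visit is a covariate, power is already about 0.89.

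**Conclusion.** The point holds as a missed efficiency gain. Two protocol-standard SBP measurements exist before randomisation for every enrolled patient and have no stated role beyond eligibility. The planned comparison is valid without them, and the plan's power figure is approximately reproduced.

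Beyond single-visit adjustment, the gain is most plausibly 3-10% of residual variance. The outer limits are 2-4% under one reading of the reliability figure and about 20% under perfect tracking. In power at 6 mm Hg and ρ = 0.5, the screening visits add about 1 to 5 points, whereas moving from the unadjusted change analysis to baseline-visit adjustment adds about 10. These results rest on the plan's SD, correlation, reliability and clustering figures, on an assumed between-visit correlation, and on no dropout.

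**What to change.** In the primary model for 6- and 12-month SBP, include as covariate the mean SBP of the three pre-randomisation visits (two screening, one baseline), with a covariate-by-visit term, and read the 12-month arm difference from the group-by-visit term. Under randomisation this targets the same between-arm difference as the comparison of change. Keep the baseline-visit value alone for descriptive change from baseline: the screening values are selected at 140 mm Hg or above, so averaging them into that change would build in regression to the mean.

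The cost is a few degrees of freedom and no new data. The Analytic plan's statement that the main analyses carry no covariates would have to be amended and the mixed model re-specified, before any unblinded outcome data are seen. If the sponsor prefers less change, adjusting for the baseline visit alone secures most of the benefit.

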#### Randomization

Once baseline assessments are completed, all relevant records related to the patient’s stroke admission are abstracted from the EHR and sent to the adjudication committee for review. Once the adjudicators have confirmed the diagnosis of stroke, the Research Core performs the randomization procedure. The RA informs the patient of the assigned study arm and enters him/her into the telehealth web portal, which triggers delivery of the HBPTM device to the patient’s home and contact from a NCM. Randomization is within primary care physician on a 1:1 assignment to the two treatment arms.

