### Treatment fidelity

Our efforts to maximize the quality and consistency of the interventions include (1) careful training of patients in the use of the home BP monitors; (2) strategies to enhance patient adherence to each of the interventions (that is, reminder calls, monitoring transmission of home BP readings, weekend availability for NCM sessions); and (3) monitoring of adherence to the interventions to evaluate consistency across study sites and, for the HBPTM + NCM arm, across nurses. A key strength of this study is the use of an established, successful NCM intervention that does not require extensive training or supervision from research staff, aside from details of the study protocol. The nurses working with the House Calls program have undergone extensive training in principles and strategies of behavior change needed for effective counseling of chronic disease patients (for example, motivational interviewing skills, problem-solving approaches). To provide data on intervention content for secondary analyses, the nurses complete a checklist following each counseling session to indicate the topics covered.

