#### Summary

Conservatively, under the assumptions specified above, 225 subjects per group will provide power ≥0.80 to detect the hypothesized 6 to 8 unit differential change in SBP, based on testing the Time X Group interaction in a mixed model, adjusting for unreliability, design effects due to clustering and serial correlations. This sample size will also provide power ≥ 0.80 to detect the hypothesized 10% group reduction in the rate of stroke at 24 months from a baseline rate of 15%.

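### The power calculation inflates for PCP clustering as if whole PCPs were randomised, although patients are randomised within PCP (a conservative error), and has no term for clustering by counselling nurse

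*Protocol article*

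**What the plan says.** Under Randomization, the Protocol article states: "Randomization is within primary care physician on a 1:1 assignment to the two treatment arms". Each PCP can therefore contribute patients to both arms.

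Under Sample size and power analysis, the cluster is the PCP; the number of eligible patients "within PCP is estimated to range from 5 to 6". The inflation is then given as "The cluster size was estimated as 5; the intracluster correlation (ICC) = 0.03; and Vif = 1+ (clustersize-1)*ICC = 1.12". The other inputs are "α = .05 for a two-tailed test; 1-β = .80 and above", "δ = μ_1_-μ_2_ = 6, 7, 8 (SBP point reduction" and "pooled σ = 20.75", with reliability R = 0.90. The stroke recurrence calculation carries over the same reliability, cluster size and ICC. The Summary presents 225 per group as sufficient after "adjusting for unreliability, design effects due to clustering and serial correlations".

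On nurses, the article describes a year-long call schedule for the HBPTM + NCM arm: weekly in months 1 to 2, every two weeks in months 3 to 4, monthly in months 5 to 12. That is roughly 8 + 4 + 8 = 20 calls, with more allowed at the nurse's discretion. HBPTM-alone patients have an early nurse contact about the device and the educational materials, and no counselling schedule. Treatment fidelity includes "monitoring of adherence to the interventions to evaluate consistency across study sites and, for the HBPTM + NCM arm, across nurses". No power section mentions nurses.

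**The concern.** The formula 1 + (m − 1) × ICC describes a design in which all patients of a PCP share one arm. Differences between PCPs then add to the variance of the treatment contrast. When both arms sit inside each PCP, those differences largely drop out. The article's power statement therefore rests on a design effect that does not belong to its own randomisation.

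The level at which patients in one arm do share a source of variation is the counselling nurse. Patients of the same nurse may have correlated outcomes because of that nurse's skill or intensity, and randomisation within PCP does not remove this. The article recognises possible variation between nurses in its fidelity plan but carries nothing of it into the power calculation. At stake are whether 225 per group is justified by the right quantities and, depending on the model finally fitted, whether the standard error of the SBP comparison is large enough.

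**Working it through.** **Inputs from the Protocol article:** m = 5 (range 5 to 6), ICC = 0.03, σ = 20.75, R = 0.90, two-sided α = 0.05, power 0.80, δ = 6, 7, 8, n = 225 per group.
**Assumed, not in the article:** 5, 10 or 20 nurses; nurse ICC 0.01 to 0.03; equal caseloads.

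**1. The plan's own figures.**
- 1 + 4 × 0.03 = 1.12, as stated (1.15 at m = 6). The arithmetic is right.
- The root mean square of the six listed SDs is 20.745, which agrees with 20.75.
- n per group = 2 × (1.960 + 0.842)² × 20.75² / δ² = 187.7 at δ = 6 and 137.9 at δ = 7. Multiplying by 1.12 and dividing by 0.90 gives 234 and 172, close to the stated 175 to 225. Dividing by R is my reading of how reliability was used. This n also equals that for a change score with ρ = 0.5, since 2(1 − ρ) = 1.

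**2. The PCP factor under the stated randomisation.** For assignment within PCP the factor is (1 − ICC) + ICC × D/m, where D is the mean squared difference between the numbers in the two arms within a PCP.
- Exact balance: D = 0, factor 0.97.
- Five patients split 2:3 or 3:2: D = 1, factor 0.97 + 0.03/5 = 0.976.
- No balancing at all: D = m, factor 1.00.
- Whole PCPs in one arm: D = m², factor 0.97 + 0.03 × 5 = 1.12, the article's value.

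Simulations of 90 PCPs with five patients each scatter around these values (0.96 to 1.01 for assignment within PCP, 1.10 to 1.13 for whole PCPs), with a Monte Carlo error of two to three percentage points.

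**3. Effect on n and power.** 1.12/0.97 = 1.155, so n is overstated by about 15% (12% with no balancing).
- δ = 6: 187.7 × 0.97/0.90 gives 203 per group instead of 234.
- δ = 7: 137.9 × 0.97/0.90 gives 149 instead of 172.
- Power at 225 per group, δ = 6, as Φ(δ/SE − 1.96) with SE = √(2 × 20.75² × factor/225): factor 1.12/0.90 gives 0.785; factor 0.97/0.90 gives 0.840.

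**4. Nurse clustering in one arm.** With k nurses, the design effect in the HBPTM + NCM arm is DE = 1 + (225/k − 1) × ICC. The variance of the arm difference is multiplied by A = (1 + DE)/2. If the model ignored nurse, the true two-sided error would be 2 × [1 − Φ(1.96/√A)]. The PCP factor is set to 1 here.

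| Nurses | Nurse ICC | DE | A | Power, δ = 6, no R | Power, δ = 6, R = 0.90 | Error if nurse ignored |
|---|---|---|---|---|---|---|
| 5 | 0.01 | 1.44 | 1.22 | 0.793 | 0.750 | 7.6% |
| 5 | 0.03 | 2.32 | 1.66 | 0.663 | 0.617 | 12.8% |
| 10 | 0.01 | 1.22 | 1.11 | 0.830 | 0.790 | 6.3% |
| 10 | 0.03 | 1.65 | 1.32 | 0.760 | 0.716 | 8.8% |
| 20 | 0.01 | 1.10 | 1.05 | 0.849 | 0.810 | 5.6% |
| 20 | 0.03 | 1.31 | 1.15 | 0.815 | 0.773 | 6.8% |

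**5. Does the surplus 12% cover it?** Setting A = 1.12 gives ICC = 0.24/(225/k − 1): about 0.005 with 5 nurses, 0.011 with 10 and 0.023 with 20.

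**6. Other corners of the plan's grid (no R).** With 5 nurses and ICC 0.03, power is 0.79 at δ = 7 and 0.89 at δ = 8. At δ = 6 with ρ = 0.6, it is 0.76 to 0.87 with 5 nurses and 0.85 to 0.90 with 10, over ICC 0.03 down to 0.01.

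**The case against.** The strongest reply is that the only error shown from the text is on the safe side. Using 1.12 where about 0.97 applies asks for more patients than needed and costs neither power nor type I error; the Summary itself calls its result conservative. That stands. A treatment-by-PCP interaction could justify some inflation, but the article does not invoke one.

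Second, a reader might infer from the missing nurse term that the trial is underpowered. The article does not support this. It gives neither the number of nurses nor a nurse ICC, and δ = 6 with ρ = 0.5 is the least favourable corner of its grid. With 20 nurses the variance rises by only 5% to 15%, and the surplus 12% absorbs most of that range.

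Third, a reader might infer that the planned SBP test has an inflated type I error. That does not follow either. The Analytic plan says the mixed model can accommodate clustering and different residual variances by group, without naming a level. Naming random effects is ordinary content for an analysis plan, which is not shown. The error rates above hold only if patients of one nurse were analysed as independent.

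Finally, nurse contact is not confined to one arm; only the counselling schedule is. What remains is that the PCP factor is the wrong one for the stated design, and that its accidental surplus is no reliable substitute for a nurse term. With 5 or 10 nurses it is used up at quite small nurse ICCs, and spare sample size does not correct a standard error that omits nurse.

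**Conclusion.** The concern holds in two parts of different strength.

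The PCP part follows from the article alone. The factor 1.12 contradicts randomisation within PCP; the right value is about 0.97, and no more than about 1 even if balance within PCP were left to chance. Required n is overstated by about 15%, and the same input feeds the stroke recurrence calculation. The error is conservative.

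The nurse part is a real design feature without a term in the calculation, but its size is conditional. For 5 to 20 nurses and ICC 0.01 to 0.03, the variance of the arm difference rises by about 5% to 66% and power at 6 mm Hg is about 0.66 to 0.85 without the reliability factor. If nurse were ignored in the SBP model, the true error would be about 5.6% to 12.8%. The two parts act in opposite directions, so their net effect on 225 per group is undetermined. The stated justification needs correcting; inadequacy of the sample size is not demonstrated.

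**What to change.** - Replace 1.12 with the within-PCP factor (1 − ICC, or the value matching the actual balance within PCP) and restate power for SBP and for stroke recurrence.
- Keep PCP, the unit within which patients are randomised, as a random intercept in the SBP model.
- State the expected number of nurses and report power over a stated range of nurse numbers and nurse ICCs.
- Fit the SBP model with a nurse random effect in the HBPTM + NCM arm only, with small-sample degrees of freedom, as the primary model or a prespecified sensitivity analysis.
- Record the nurse ID for each patient. The article says that nurses enter encounter notes in the web portal, but not that nurse identity is held as a data field, so this should be confirmed.

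The cost is a recalculation, one model term and one data item. The statistical price is a wider confidence interval if nurses differ, appreciably so with few nurses. With 5 nurses and ICC 0.03, the Satterthwaite degrees of freedom are about (1 + 2.32)²/(2.32²/4 + 1/224) = 8, and power at 6 mm Hg falls to about 0.56 rather than the 0.66 given by normal quantiles.
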